## Abstract

**Background:**

Depression that occurs during the perinatal period has substantial costs for both the mother and her baby. Since in-person care often falls short of meeting the global need of perinatal women, Internet interventions may function as an alternate to help women who currently lack adequate access to face-to-face psychological resources. However, at present there are insufficient empirically supported Internet-based resources for perinatal women.

**Objective:**

The aim of this study is to compare the relative efficacy of Internet-based cognitive behavioral therapy (CBT) to a novel Internet-based compassionate mind training approach (CMT) across measures of affect, self-reassurance, self-criticizing, self-attacking, self-compassion, depression, and anxiety. While CBT has been tested and has some support as an Internet tool for perinatal women, this is the first trial to look at CMT for perinatal women over the Internet.

**Methods:**

Participants were recruited through Amazon Mechanical Turk (MTurk) and professional networks. Following completion of demographic items, participants were randomly assigned to either the CBT or CMT condition. Each condition consisted of 45-minute interactive didactic and follow-up exercises to be completed over the course of two weeks.

**Results:**

Post course data was gathered at two weeks. A 2x2 repeated measures analysis of variance will be conducted to analyze differences between conditions at post course.

**Conclusions:**

The implications of the trial will be discussed as well as the strengths and limitations of MTurk as a tool for recruitment. We will also briefly introduce the future directions along this same line of research.

**Trial Registration:**

ClinicalTrials.gov NCT02469324; https://clinicaltrials.gov/ct2/show/NCT02469324 (Archived by WebCite at http://www.webcitation.org/6fkSG3yuW)

## Introduction

Mood changes during and after pregnancy are common although they do not always result in clinically significant depressive episodes. However, both severe and the moderate/milder forms of depression during the perinatal period and postnatal can be a source of major problems to mothers, their babies, and even other family members. Symptoms of postpartum depression (PPD) include, but are not limited to, concentration difficulties, poor sleep, heightened anxiety, feelings of inadequacy, ruminative fears and compulsive thoughts, loss of attachment sentiments, and guilt feelings [1]. The physiological effects of prenatal depression such as elevated cortisol can adversely affect the baby’s development and result in negative consequences that remain undetected into adulthood [2].

The costs of PPD, both for the mother and her child, are concerning, especially since the incidence of PPD reaches 7.1% in the United States (US) and is as high as 19.2% when minor depressive episodes are included [3]. It is estimated that the global incidence of PPD is even higher than within the United States [4], suggesting a pressing global health concern for women and their children. Additionally, there is research that demonstrates a relationship between lower income areas and higher PPD prevalence [5], demonstrating that communities who already lack access to adequate health and mental health resources are further affected by untreated PPD in their communities.

Even though the human and financial costs of untreated PPD are well-established, adequate resources to address the global need of women suffering from PPD or who are at risk of developing PPD do not yet exist. Presently, the first line of psychological treatment for PPD is cognitive behavioral therapy (CBT). However, in a review of five randomized controlled trials (RCTs) comparing CBT with standard postpartum care, only two trials demonstrated better outcomes in the CBT group [6]. While preliminary Interpersonal Therapy (IPT), with a focus on handling the interpersonal disputes that occur during childbirth and childcare, has shown some promise in addressing this pressing need [7]. The first line of treatment for PPD continues to be medication [8], particularly selective serotonin reuptake inhibitors (SSRIs), which show some level of efficacy and perform equal to psychotherapy in randomized trials [8,9]. However, there are concerns regarding the safety of antidepressants for pregnant and nursing women [10].

There are many practical limitations to treatment seeking, not least being the availability of appropriately qualified therapists. In addition, issues such as stigma, childcare difficulties, lack of knowledge, and financial constraints can inhibit help seeking [11]. As such, psychological resources that do not require women to leave their homes may allow for more women to participate in psychological interventions. In general, Internet interventions can be private and used anonymously, accessed repeatedly at any time, and from any location, and Internet interventions may provide a much-needed service to users who feel marginalized or stigmatized [12]. Clatworthy’s [13] meta-analysis did not find a relationship between the length of an in-person preventative intervention and its effectiveness, suggesting that increasing the length of psychological interventions is not an important factor in enhancing benefit. However, there is research to show that interventions based on psychological models tend to be more effective than interventions that are not based on these models [13], meaning that researchers seeking to create new resources for women should maintain fidelity to empirically supported psychological models.

As a result of the limitations that preclude many women from seeking in-person resources, Internet interventions offer promise in providing care with less financial and practical barriers. Additionally, Internet interventions can be used as adjuncts to in-person treatments or replacements in other cases [14], and perhaps offer even more promise for reducing health disparities. Nonconsumable interventions, or those that can be reused with minimal cost for each additional participant, can help to close the gap in services through offering assistance without needing the support of a clinician or operator on the other end [15]. Currently, there is a dearth of research on Internet interventions for perinatal women or to address PPD [16].

Importantly, over the last 20 years different psychotherapies have been developed that are increasingly rooted in the scientific understanding of psychological processes, including those associated with attachment. For example, compassion focused therapy (CFT) is based on evolutionary insights of brain function, particularly the importance of building and developing affiliative and prosocial relationships with self and other [17,18]. This model in particular articulates the role of affiliative emotion and motivation in threat regulation and how these can be cultivated through (1) addressing issues of self-criticism and shame and (2) with affiliation building exercises (compassion cultivation). This is important because at the heart of many depression difficulties is a harshly self-critical relationship with the self and at times nonaffiliative relations with self and with others. In addition, helping to build affiliative relationships between mothers and their babies is obviously important. There is now considerable evidence that compassion cultivation has an impact on a range of physiological systems including the immune system, frontal cortex, and cardiovascular systems [19]. It also promotes prosocial and empathic behavior [20]. This makes compassion cultivation an especially important focus for intervention for this population.

The present study therefore seeks to assess the efficacy of an Internet-based Compassionate Mind Training (CMT) program, the intervention component of CFT, compared to a standard CBT program in a sample of childbearing and perinatal women. As there is currently a lack of Internet interventions for maternal mental health, the research team intends to assess the relative efficacy of CMT as a resource for women during this period.

It is expected that participants randomized to both Internet-based CMT and CBT will demonstrate improved affect as well as reduced depression and anxiety at similar, if not better, levels which are the secondary outcome measures of this trial. However, in terms of the primary outcome measures, we expect that Internet-based CMT will provide unique benefit above and beyond CBT in the constructs of self-reassurance, self-criticizing, self-attacking, and self-compassion, as CMT is specifically targeted towards these constructs.

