## Methods

### Participants and Procedures

Participants were recruited through two primary sources: online through Amazon Mechanical Turk (MTurk) and through professional networks. Recruitment for the present study occurred between April 2015 to September 2015.

Upon navigating to the landing page, participants were asked to review and agree to informed consent (IC) before beginning the study. For a copy of the IC for the present study, see Multimedia Appendix 1. Participants who met criteria for inclusion were then randomized to either the CBT (n=60) or CMT (n=60) condition. As the trial was designed to assess the efficacy among perinatal women of an Internet-based CMT relative to an Internet-based CBT intervention, a control group was not employed. To ensure equivalent numbers of participants were randomized to both conditions, an embedded algorithm was used.

Each condition was divided into equal parts (a) and (b) with condition-specific content reflective of the theoretical orientation of the intervention. In part (a), participants completed a didactic, which included written materials and brief experiential exercises. The didactic portion of the course provided an introduction to the approach and was created to take approximately 45 minutes to complete. Following completion of part (a), participants received an automatically generated email based on their assigned condition. The email included follow-up exercises for the CBT condition and audio meditations for the CMT condition. At this point, participants were informed that they would receive additional emails at Day 4, Day 7, and Day 14 of the course.

Based on a power analysis to detect an effect of .4 at alpha .05 with 80% power, this study needed to include a minimum of 23 participants for each condition who complete the post course assessment at two weeks. The standardized effect size was estimated using [21] and the meaning of this size is .25 for small, .5 for medium and 1.00 for large. The designated medium effect size is consistent with what is universally agreed upon in published mindfulness research [22]. However, the research team tried to recruit 60 participants for each condition in order to account for attrition that is inherent in clinical trial, especially ones conducted over the Internet.

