### Analysis

The present study seeks to compare the efficacy of two theoretical approaches using a randomized conditional approach with outcome comparisons at baseline, throughout the course period, and at the post course two weeks following randomization. Pre course equivalence between participants in each condition will follow analytical procedures recommended by the CONSORT 2010 Statement [29]. A 2x2 mixed analysis of variance (ANOVA) will be run for each measure at baseline and follow-up. The between subjects factor in the ANOVA will be condition and the within subjects factor will be the outcome measure. A main effect of time and a main effect of condition will be analyzed to determine if there is a difference between CBT and CMT on each of the outcome measures.

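### A test for a difference with no margin cannot support the expectation that CMT and CBT do similarly well on affect, depression and anxiety

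*Protocol article*

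**What the plan says.** The last paragraph of the Introduction sets out two kinds of hypothesis. For the primary outcomes (self-reassurance, self-criticizing, self-attacking, self-compassion) it expects CMT to outperform CBT. For the secondary outcomes it expects that participants in both arms "will demonstrate improved affect as well as reduced depression and anxiety at similar, if not better, levels".

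The Analysis section gives one method for all measures: "A 2x2 mixed analysis of variance (ANOVA) will be run for each measure at baseline and follow-up". It continues: "A main effect of time and a main effect of condition will be analyzed to determine if there is a difference between CBT and CMT". The article states no margin, equivalence test or non-inferiority test, and this section does not name the condition-by-time interaction.

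On design, Participants and Procedures says that "a control group was not employed", because the aim is efficacy relative to CBT. It asks for at least 23 completers per condition at two weeks and gives 60 randomized per condition. Under Outcome Measures, affect is rated at baseline and just after the didactic, while the PHQ-4 is given before the didactic and at two weeks.

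**The concern.** The secondary hypothesis has two halves, and the stated analysis fits neither.

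- **Similarity between arms.** A test for a difference can support the claim that the arms differ. It cannot support the claim that they are alike, because non-significance also arises from imprecision and becomes more likely as completers fall. With no margin, no stated result could show the two courses to be similar. At stake is a materially worse CMT result passing as parity with CBT on depression and anxiety.
- **Improvement in both arms.** This half rests on the main effect of time. With no untreated arm, that effect combines any course effect with retesting, demand and natural change. Parity with CBT would not settle the matter either: the Introduction reports that, of five trials of CBT against standard postpartum care, "only two trials demonstrated better outcomes in the CBT group".

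**Working it through.** **Inputs.** From Participants and Procedures: alpha 0.05 (taken as two-sided, since the article does not say), an effect of 0.4, 23 completers per arm and 60 randomized per arm. Assumed, because the article gives no value: SD = 1 at each time, equal baselines, and a pre-post correlation r of 0.3 to 0.7 (0.5 for baseline adjustment).

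**The plan's own figure.** The article bases its sample size on a calculation: "Based on a power analysis to detect an effect of .4 at alpha .05 with 80% power". For a standardized mean difference, n per arm = 2(1.96 + 0.842)²/0.4² = 98.1, so 99, not 23. That mismatch is a separate matter. The figures below use 23 and 60 only as the stated sample sizes.

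**1. The effect the article names: main effect of condition.** This compares the arms on the average of the two time points.
- A 0.4 SD post-course deficit with equal baselines becomes 0.4/2 = 0.2 SD on the average.
- The SD of the average is √((1+r)/2), so the standardized effect is 0.2/√((1+r)/2): 0.248 at r = 0.3, 0.231 at r = 0.5 and 0.217 at r = 0.7.
- The probability of non-significance (noncentral t, noncentrality d√(n/2), 2n−2 df) is shown below.

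| r | 23 per arm | 60 per arm |
|---|---|---|
| 0.3 | 87% | 73% |
| 0.5 | 88% | 76% |
| 0.7 | 89% | 78% |

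**2. More suitable comparisons, same 0.4 SD deficit.**

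| Comparison | Standardized effect | 23 per arm | 60 per arm |
|---|---|---|---|
| Post score only | 0.40 | 74% | 42% |
| Baseline-adjusted, r = 0.5 | 0.4/√(1−0.25) = 0.46 | 67% | 29% |

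The condition-by-time interaction is a comparison of change scores, whose SD is √(2(1−r)). At r = 0.5 that SD is 1, so the interaction gives the same figures as the post-score row.

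**3. Precision.** The 95% CI half-width is 1.96√(2(1−r²)/n).
- 23 per arm: 0.58 SD unadjusted, 0.50 SD with r = 0.5.
- 60 per arm: 0.36 SD unadjusted, 0.31 SD with r = 0.5.

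The article's own scale calls 0.25 small and 0.5 medium. If the observed difference is near zero, an interval at 23 per arm therefore extends to a medium deficit or beyond.

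**4. What a margin-based claim would face.** The margins are assumptions. Power for non-inferiority with a true difference of zero and one-sided alpha 0.025 is Φ(m/√(2/n) − 1.96), unadjusted.

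| Margin m (SD) | 23 per arm | 60 per arm | n per arm for 80% |
|---|---|---|---|
| 0.3 | 17% | 38% | 175 |
| 0.4 | 27% | 59% | 99 |
| 0.5 | 40% | 78% | 63 |

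**5. Which n applies.** The 23-per-arm minimum is defined by completion of the two-week assessment, so it governs the PHQ-2 and GAD-2. Affect is collected right after a didactic of about 45 minutes, so its available n is not set by that minimum.

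**The case against.** The strongest reply is that the article nowhere says a null result will be called similarity. The wording is an expectation about secondary outcomes, not a declared non-inferiority objective. The primary hypothesis is superiority, for which a difference test is the right kind. The article calls itself a preliminary pilot and condenses a fuller plan, so a missing margin or CI alone would be no finding. All of this stands, and it limits the weight of the point. What remains is a conflict between two stated texts: a hypothesis that the arms do well "at similar, if not better, levels", and an analysis run "to determine if there is a difference between CBT and CMT on each of the outcome measures".

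A reader might infer four stronger things that the documents do not support.

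- **That the team plans to report non-significance as parity.** This is a risk, since no other route to the claim is stated, but it is not a documented intention.
- **That the missing control arm is an undisclosed flaw.** It is disclosed and fits the relative aim. The Discussion also says decisive conclusions about CMT's treatment effectiveness cannot be drawn. That caveat helps only in part: its reason is that women were not recruited on depression status, and it does not address a claim of similarity to CBT.
- **That regression to the mean would drive the time effect.** Women were enrolled regardless of depression status, so this is minor. For affect, natural change within a session of about 45 minutes is also a weak explanation. Retest and demand effects remain.
- **That no margin below about 0.5 SD could be excluded at 23 per arm.** Exclusion depends on the point estimate as well as the half-width. The chance is low (17% at a 0.3 SD margin, 27% at 0.4 SD), not nil.

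**Conclusion.** The point holds as a mismatch between the secondary hypothesis and the stated test. A non-significant ANOVA result cannot support similarity on affect, depression or anxiety. Given a true 0.4 SD post-course deficit and equal baselines, the condition main effect that the article names would usually miss it, even with all 60 per arm. A post-score or adjusted comparison does better but still misses it often. These figures rest on assumed correlations, SD = 1 and two-sided testing. The 23-per-arm figures apply to the PHQ-4 subscales only.

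A significant CMT advantage in change would still support the claim of better, and the time effect remains a valid description of pre-post change. The weight is moderate: these are secondary outcomes in a pilot, and the remedy lies in analysis and wording.

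**What to change.** Recruitment has ended, but the analysis is still described in the future tense, so the change needs no new participants.

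- For affect, PHQ-2 and GAD-2, estimate the CMT-CBT difference by baseline adjustment or the condition-by-time term, and report it with a 95% CI.
- Fix and justify a margin for each measure before analysis. Claim similar or better only if the CI excludes a CMT deficit of that size. Otherwise report the result as inconclusive, and do not infer similarity from non-significance.
- Describe the main effect of time as pre-post change that cannot be attributed to either course, given the absence of an untreated arm.
- If no margin can be justified, reword the secondary hypothesis as estimation of the between-arm difference alongside descriptive change.

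The cost is the choice of a margin and a weaker permitted claim. At these sample sizes, inconclusive is a likely result for any margin much below 0.5 SD.

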## Methods

### Participants and Procedures

Participants were recruited through two primary sources: online through Amazon Mechanical Turk (MTurk) and through professional networks. Recruitment for the present study occurred between April 2015 to September 2015.

Upon navigating to the landing page, participants were asked to review and agree to informed consent (IC) before beginning the study. For a copy of the IC for the present study, see Multimedia Appendix 1. Participants who met criteria for inclusion were then randomized to either the CBT (n=60) or CMT (n=60) condition. As the trial was designed to assess the efficacy among perinatal women of an Internet-based CMT relative to an Internet-based CBT intervention, a control group was not employed. To ensure equivalent numbers of participants were randomized to both conditions, an embedded algorithm was used.

Each condition was divided into equal parts (a) and (b) with condition-specific content reflective of the theoretical orientation of the intervention. In part (a), participants completed a didactic, which included written materials and brief experiential exercises. The didactic portion of the course provided an introduction to the approach and was created to take approximately 45 minutes to complete. Following completion of part (a), participants received an automatically generated email based on their assigned condition. The email included follow-up exercises for the CBT condition and audio meditations for the CMT condition. At this point, participants were informed that they would receive additional emails at Day 4, Day 7, and Day 14 of the course.

Based on a power analysis to detect an effect of .4 at alpha .05 with 80% power, this study needed to include a minimum of 23 participants for each condition who complete the post course assessment at two weeks. The standardized effect size was estimated using [21] and the meaning of this size is .25 for small, .5 for medium and 1.00 for large. The designated medium effect size is consistent with what is universally agreed upon in published mindfulness research [22]. However, the research team tried to recruit 60 participants for each condition in order to account for attrition that is inherent in clinical trial, especially ones conducted over the Internet.

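### The stated 23 completers per condition do not give 80% power for a between-arm effect of .4; unadjusted power is about 26%, and 80% needs a difference near 0.85 SD

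*Protocol article*

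**What the plan says.** The only sample-size justification is in Methods, Participants and Procedures. It says that, "to detect an effect of .4 at alpha .05 with 80% power, this study needed to include a minimum of 23 participants" per condition, counted as those who finish the two-week assessment. It calls the effect standardized and says that "the meaning of this size is .25 for small, .5 for medium and 1.00 for large". It then adds: "The designated medium effect size is consistent with what is universally agreed upon in published mindfulness research". No sidedness, test or pre-post correlation is given. Sixty per condition were sought, and the reason given is attrition.

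The Introduction states the primary hypothesis as a between-arm one: CMT is expected to do better than CBT on self-reassurance, self-criticizing, self-attacking and self-compassion. The Analysis section plans a 2x2 mixed ANOVA on baseline and follow-up for each measure. The Discussion describes the study as preliminary and as a pilot.

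**The concern.** Benchmarks of .25, .5 and 1.00 for a standardized effect belong to a standardized mean difference. On that scale 23 per arm is far too few for an effect of .4. The text also treats .4 as the medium effect directly after giving .5 as medium.

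The statement presents 23 completers as enough. The comparator is an active treatment, so a modest between-arm difference is realistic. If the 80% claim is taken at face value, a non-significant CMT–CBT result from a few dozen completers could be read as showing that the two courses perform alike. At 26% power, a true difference of 0.4 SD would be missed about three times in four.

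**Working it through.** **Inputs from the article:** effect .4, alpha .05, power 80%, 23 completers per arm, 60 per arm recruited with 1:1 allocation. **Assumptions:** SD = 1 (standardized scale); two-sided test, with one-sided shown as well; pre-post correlation ρ not given, so a range is used.

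**1. Trying to reproduce 23.** The normal approximation for two means is n per arm = 2(z₀.₉₇₅ + z₀.₈₀)²/d² = 2(1.960 + 0.842)²/0.4² = 98.1, so 99. The exact noncentral t gives 100. One-sided, it gives 78. The stated 23 does not reproduce.

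**2. Power at the stated numbers.** The noncentrality is d·√(n/2), with 2n − 2 degrees of freedom.
- n = 23: 0.4 × √11.5 = 1.356, 44 df. Power is 26.4% two-sided and 37.9% one-sided.
- n = 60: 0.4 × √30 = 2.191, 118 df. Power is 58.4% two-sided and 70.3% one-sided.

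**3. Detectable difference at 80% power, two-sided, unadjusted.** 0.845 SD at 23 per arm (0.745 one-sided) and 0.516 SD at 60 per arm.

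**4. The article's own medium value, d = .5.** 64 per arm are needed; 23 per arm give 38%.

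**5. Using baseline, as the planned ANOVA does.** The condition-by-time test in a 2x2 design is equivalent to comparing change scores. The effective d is 0.4/√(2(1 − ρ)) for change scores and 0.4/√(1 − ρ²) for ANCOVA.

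| ρ | Change score, 23/arm | ANCOVA, 23/arm | Change score, 60/arm | ANCOVA, 60/arm |
|---|---|---|---|---|
| .5 | 26% | 34% | 58% | 71% |
| .7 | 40% | 46% | 80% | 86% |

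For example, with change scores at ρ = .7 the effective d is 0.4/√0.6 = 0.516. Power of 80% at 23 per arm requires ρ = .888 (change score) or .881 (ANCOVA).

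**6. Other readings of .4 that come near 23.**
- *One-way Cohen's f = .4:* with two groups d = 2f = 0.8, which needs 26 per arm; 23 give 76%.
- *Repeated-measures between-arm f = .4:* 46 in total give 81% at ρ = .75 and 80% at ρ = .8. This is a 0.8 SD difference averaged over both time points. Randomization makes the expected baseline difference zero, so it implies 1.6 SD at follow-up.
- *Correlation r = .4:* about 47 in total, but d = 2(.4)/√(1 − .16) = 0.87.
- *Main effect of time, arms pooled (46 people):* a pre-post change of 0.4 SD has 80% power at ρ = .55 and 84% at ρ = .6. This tests change over time, not CMT against CBT.

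Each of these either implies a between-arm difference of about 0.8 SD or more, or tests a different contrast.

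**The case against.** The strongest objection is that the article names no metric, test or correlation, so a slip in calculation cannot be proved. Step 6 shows several calculations that return roughly 23 per arm, and the pooled time effect does so at an ordinary correlation. An article may also leave such detail to a fuller protocol. This stands as far as the origin of the number goes: a reader might infer a plain miscalculation, and the document cannot confirm that. It does not save the statement. The text gives effect, alpha, power and n together, on a scale of its own, and they do not fit the contrast that the trial was set up to test.

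A second tempting inference is that the trial is underpowered even with all 60 per arm. The documents do not support this. The 58% is an unadjusted figure, while the planned analysis uses baseline; at a correlation of .7, 60 completers per arm give 80–86%. Likewise, 100 per arm is an unadjusted requirement; at the same correlation it falls to 60 (change score) or 52 (ANCOVA).

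Third, 23 refers to people completing the two-week assessment. Among the primary constructs, only self-compassion is measured then. The FSCRS is given before and after the didactic, so its sample is those who finish that part, and its pre-post correlation over so short an interval may be high (an assumption; no value is given). The power statement makes no such distinction.

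Finally, a reader might infer that the authors intend to treat a null result as informative. They do not say so, and the Discussion already calls the study a preliminary pilot that cannot support decisive conclusions about treatment effectiveness. That limits the harm but leaves the 80% figure uncorrected. Calling .4 medium is minor in itself, since .4 is closer to .5 than to .25.

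**Conclusion.** The point holds for the claim about 23 completers per arm. For a between-arm difference of 0.4 SD, power is about 26% unadjusted and two-sided, 38% one-sided, and between 26% and 46% when baseline is used with a correlation of .5 to .7. Reaching 80% takes a correlation of about .88–.89, which the article does not state, or a difference of about 0.85 SD, which is nearer the article's large value than its medium one. These results rest on reading .4 as a standardized mean difference, which the article's benchmarks indicate, and on the CMT-versus-CBT contrast being the one that is powered, as the primary hypothesis implies. The conclusion does not extend to the adequacy of 60 per arm, which depends on the unstated correlation and on attrition.

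**What to change.** Replace the power sentence with wording such as:

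*23 completers per arm give 80% power (two-sided alpha .05) for an unadjusted between-arm difference of about 0.85 SD. A difference of 0.4 SD needs about 100 per arm unadjusted. Sixty completers per arm detect about 0.52 SD unadjusted, or about 0.4 SD in a change-score (condition-by-time) analysis if the pre-post correlation is about .7.*

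Alongside it:
- name the effect-size metric, the test, the sidedness and the assumed correlation;
- reconcile the .4 with a scale on which medium is .5;
- report between-arm estimates with 95% confidence intervals, and do not read a non-significant difference as equivalence.

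Recruitment has ended and no extra participants are needed. The cost is rewording and a less favourable stated figure.
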